### Outcomes

#### Primary Outcome

##### Key Workers’ Self-Efficacy in Supporting Parental Mental Well-Being

We have developed a set of items to measure how confident key workers are in supporting parental mental well-being. A total of 10 items measured on a visual analogue scale (VAS; Multimedia Appendix 1) assess perceived confidence in understanding and supporting parental mental well-being; their knowledge about how to support parents’ well-being and refer parents for additional help; and to communicate with parents about their well-being based on Bandura’s [46] recommendation that self-efficacy questionnaires are task-specific. The items tapping the same domain of efficacy will be correlated with each other and averaged. The primary analysis will be conducted on the average, with each item given equal importance for each individual at each assessment, of the 10 VAS measurements denoting key worker confidence (KWC).

#### Secondary Outcomes

##### Managers’ Self-Efficacy in Supporting Key Workers’ Well-Being

We also developed a set of items, using the scale recommended by Bandura, to measure the perceived confidence of managers in supporting key workers’ well-being in the workplace and to support their staff to adequately support parental mental well-being (Multimedia Appendix 1). A total of 10 items measured on a VAS assess their perceived confidence in understanding, identifying, and supporting staff well-being and workplace stress and in initiative debriefing after a potentially stressful workplace event. The items tapping the same domain of efficacy will be correlated with each other, summed, and averaged. The primary analysis will be conducted on the average, with each item given equal importance for each individual at each assessment, of the 10 VAS measurements denoting manager confidence.

##### Parental Mental Well-Being

Parental mental well-being will be measured using the shortened Warwick-Edinburgh Mental Wellbeing Scale (WEMWBS; Multimedia Appendix 2). The WEMWBS, although less sensitive, has been shown to be reliable and valid [47], and the short 7-item version of WEMWBS was found to satisfy the strict unidimensionality expectations of the Rasch model and be largely free of bias [48]. This scale differs from other scales of mental health in that it covers only positive aspects of mental health, which was an important factor in choosing this scale to assess mental well-being in this vulnerable population. The scale uses a 5-point Likert scale and scores ranging from 1 to 5 for each item will be summed and averaged.

##### Key workers’ and Managers’ Job-Related Well-Being

Job related well-being will be measured using 2 scales as reported by Warr [49,50] (Multimedia Appendix 1).

###### Job-Related Affective Well-Being Scale

The first instrument measures job-related affective well-being using the Institute of Work Psychology Multi-Affect Indicator and includes 12 items. The staff are questioned using a 6-point Likert scale of agreement about how their job has made them feel across the multiple domains. Domain scores are provided on job related anxiety-contentment and depression-enthusiasm; this 2-dimensional model of job-related affects provides a more comprehensive view of emotional states at work than current measures of job satisfaction [51]. This scale reported acceptable internal consistency with a coefficient alpha of .78 [49].

###### Job-Related Mental Well-Being

For the second scale assessing job-related mental well-being, 9 items were selected from 2 out of 5 domains within the scale. These items were selected based on relevance to the intervention to assess self-reported job competence and negative job carry-over for staff. Excluded domains were deemed not appropriate for this evaluation. The scores between the 2 measures will be correlated, higher scores indicating greater contentment and enthusiasm as well as greater competence and negative carry-over.

##### Parent Satisfaction With Key Workers

New items were developed for this study to assess parental satisfaction with the service provided by the key workers, based on previous assessments utilized by Yooralla (Multimedia Appendix 2). A total of 5 items assess parents’ perception of support from their key worker for their social and emotional well-being and their degree of overall satisfaction with the service received from the disability provider.

##### Key Workers’ and Managers’ Perceptions of Supervisory Support

Supervisory support will be measured using some of the high-loading items of the Perceived Supervisor Support scale [52,53]. The Perceived Supervisor Support scale has 8 items based on perceptions of value and support from supervisors. A total of 3 items were chosen to assess perceived support regarding staff goals and help with problems and well-being, with most items from the scale deemed inappropriate for this evaluation. It has a high internal reliability coefficient (0.88) and has been widely used in research, including a recent project examining burnout in therapists working with children with autism [54]. These items will be averaged with each item given equal weighting.

### Process Evaluation

Process data will be collected from staff at each 3-month time point via the online survey to assess attendance, usefulness, and uptake of the intervention components, such as support-seeking behavior and use of the toolkit resources provided. Researchers will also collect data on the fidelity of the training via observation and meetings with the trainer. In addition, the focus groups being conducted at 9 months postintervention with key workers, managers, and parents will provide an opportunity to explore barriers and facilitators to the delivery of the training and translation of the skills learnt within the training to current practice. Any unanticipated outcomes will be discussed in the focus groups with staff.

### Costing of the Intervention

Cost data will be nested within the program and will be closely coordinated with the purpose and data collection of the study. The primary perspective will be that of the service provider, but health sector and client impacts will also be assessed. Cost analysis of the program, comparator, and any cost offsets will be measured based on service activity and resources required for the services to take place. Program cost will reflect the service provider’s accounting practice, for example, cost category and routine cost data collection. A template to standardize the cost data collection will be completed by each hub manager in consultation with the finance manager at baseline and repeated at 3, 6, and 9 months later. Cost offsets refer to the potential for improvement in staff productivity and/or the service provider’s revenue. Staff productivity includes staff turnover rates, absenteeism, and associated implications. The absenteeism and turnover rates can be obtained from the service provider’s records, whereas self-reported absenteeism will be measured using the short version of the World Health Organization Health and Performance Questionnaire [55,56], which will be used in conjunction with staff well-being assessment questionnaires. In addition to the key worker economic-related outcomes, the economic-related implications of parent well-being on health care system utilization will also be quantified by collecting health system resource use.

### Sample Size

The sample size (6 hubs) is pragmatically determined by the number of hubs at the service and the roll-out period for the intervention. We expect approximately 8 out of 10 key workers located at each hub to consent to be repeatedly assessed (at 0, 3, 6, and 9 months) following the start of the study and approximately 3 out of the 10 families that they each support to consent to be surveyed during the study. The effect of the pragmatically determined sample size on the power of the study was investigated as follows. With 6 hubs randomized 2 at a time every 3 months starting after baseline (0 months), we have a replicated (at the cluster or hub level) stepped-wedge design with 3 periods and we have made provision for between 6 and 8 key workers in each cluster to be repeatedly assessed across the periods. Accordingly, we expect to have between 144 and 192 observations of the primary outcome variable (KWC). KWC is measured on a bounded continuous outcome scale from 0 to 100. As a contingency, we assume that approximately 10% of the variance of a measurement on a randomly selected adult is *between-hub* variance and the remaining component of the variance of a randomly selected adult splits into *between* and *within* individual variance subcomponents according to either of the 2 scenarios—an *optimistic* intraclass correlation (ICC) of 0.5 or a *less optimistic* ICC of 0.25. As an example, the baseline mean for KWC may be 70, the total variance may be 18, and the variance components for hubs, individuals, and assessments within individuals may be 2, 4, and 12, respectively (ICC=0.25). We intend to use the method of restricted maximum likelihood (REML) to fit a linear mixed model to the observations of KWC. The model will have random effects terms for hubs, key workers within hubs and assessments within key workers (within hubs), and fixed effects terms for time (0, 3, 6, and 9 months, which span the three 3-month periods) and condition (control or intervention). On the basis of 2000 simulations of the trial for each of the 4 scenarios, we find that the minimum effect sizes that can be detected with 80% power range from 0.49 to 0.68 (Table 2). For each of the 4 scenarios, the minimum detectable effect size was calculated from 2000 simulations of the trial in which restricted maximum likelihood was used, in each simulation, to estimate the variance components, and an F test was used to compare the predicted means. As a contingency against an overall system improvement over time, each scenario also included an underlying trend over time (an increase of 2 units in key worker confidence (KWC) from the first to the last assessment). Simulations assumed baseline KWC=70, total variance=18, and between-hubs variance=2 (11.1% of the total variance) with a corresponding coefficient of variation (CV)=6.1%. Simulations were also repeated with total variance=49 and between-hubs variance=5 (10.2% of the total variance) with a corresponding CV=10%. As expected, the minimum detectable effect sizes (not shown) were very similar—a consequence of standardizing the effect difference by the square root of the total variance. Accordingly, we conclude that this study has moderate-to-high power to detect moderate effect sizes for outcome variables that are measured repeatedly on key workers.

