### Trial Design

This study employs a stepped-wedge design to evaluate the program. The design was chosen so that each hub would eventually receive the program and be provided with the new professional development opportunity. The intervention will be rolled out progressively over 9 months. The clusters for randomization will be the hubs (N=6). Randomization will be conducted by a statistician who is independent of the administration of the intervention [44]. The first 2 hubs will not be randomly selected, as senior management advised against this because of the large amount of ongoing organizational change at the service. These 2 hubs will be selected based on readiness to undergo the trial and will receive the program immediately after baseline is established with the remaining 4 hubs randomized 2 at a time, every 3 months thereafter. In this way, hubs that were previously acting as control hubs will progressively receive the program. All hubs are assessed at baseline and every 3 months thereafter. The stepped-wedge design is suitable for a phased evaluation approach such as this, in which there is an imperative to allow all participants to have access to the new program. The design also allows each hub or cluster to act as its own *pre versus post* control and, in the first 2 periods, there are at least 2 hubs acting as controls and at least 2 hubs receiving the program (Table 1). The statistical analysis (see below) will combine the *between-* and *within-* hub information on the effect of the program. We seek to minimize potential bias by not revealing to the key workers when the new program is scheduled to be allocated to their hub. However, this will be self-evident to the key workers in the last 2 hubs. Key workers that operate across multiple sites will be requested to refrain from sharing learnings or materials from the training with fellow staff at other sites who have not received the intervention. Although there is a risk of contamination, this is not anticipated to have a large effect as the number of key workers that work at multiple sites is very small.

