
### Data Analysis

#### Quantitative Analysis

The repeated measurements (4 in total) on individuals in the 6 hubs over the three 3-month periods will be analyzed using linear mixed models. For measurement scales that are not too coarse (eg, more than 7 distinct values), the statistical analyses will make use of the REML algorithm to fit the mixed model. This algorithm will take account of missing (at-random) assessments and also allows the exploration of various autocorrelation models for the repeated measurements. Comparison of the *control* and *new program* means (adjusted for period effects) will be assessed with an *F* test. If required, after inspection of diagnostic plots of residuals and fitted values, an empirical logit transformation will be used to reanalyze any item scales that are bounded and coarse. Generalized linear mixed-model techniques will be used to analyze binomial or other categorical data. Cumulative effects of exposure to the new program on key outcome variables will also be explored using the same methods. The final analysis will be conducted after all participants have had adequate opportunity to be assessed at the end of the third period (ie, at 9 months), and the database has been locked. Process evaluation will assist in the assessment of factors that impact on the feasibility, success, and sustainability of the intervention strategies and new program. A detailed statistical analysis plan can be accessed by contacting the corresponding author.

**Table 2 table2:** Minimum effect sizes.

Key workers per hub^a,b^	Intraclass correlation^c^	Minimum detectable effect size
6	0.25	0.68
6	0.5	0.56
8	0.25	0.59
8	0.5	0.49

^a^Effect size is the expected difference between the 2 conditions (intervention-control) divided by the SD (ie, the square root of the total variance).

^b^Detectable with 80% power for the proposed stepped-wedge design with 6 hubs, 3 periods, and 4 assessment time points.

^c^Intraclass correlation: between individual variance divided by the sum of the between and within individual variances.

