### Strengths and Limitations

A strength of this study is the stepped-wedged design, which allows the collection of mixed-method data, including quantitative data, also including economic data, and qualitative data from key workers and parents, which historically are a difficult cohort to involve in longitudinal research because of family demands. Particularly, the inclusion of the economic evaluation provides a model for future studies involving service delivery organizations. The design also addresses the ethical issue of conducting a blinded randomized control trial with a vulnerable population, as we deem it inequitable to provide care for mental well-being to only a cohort of parents accessing the service. A limitation of this study is that it is conducted within a changing policy and funding context, with the NDIS roll out underway in Australia, which is having an ongoing impact to service delivery within the partner organization and which we anticipate will be a potential confounder on the outcome measurements. For organizational reasons, the first 2 hubs are not randomly selected. This is not a major issue for assessment of the impact of the program on the partnering organization as we will use both this intrahub (each hub as its own control) as well as the interhub information when estimating the effect of the new program on the organization. Incomplete randomization does, however, impact on the external validity of the program. We seek to minimize potential bias by not revealing to the staff when the new program is scheduled to be allocated to their hub, although this may become self-evident in the last 2 hubs. Owing to this research being conducted in a real-world service delivery context, there is possible contamination because of a small number of key workers working across multiple sites that will receive the intervention at varying times which may not be overcome by the methods introduced to minimize contamination impact on results. Although methods to minimize the impact of this are in place, it is possible that training at 1 site will influence their service delivery approach to parents at their alternative work place that has not yet received the intervention and other staff may observe and learn, particularly because of the transdisciplinary approach. This will be addressed through discussions with relevant key workers who will be asked to avoid talking about their learnings with staff from hubs yet to receive the intervention to minimize contamination as much as possible. A further limitation of the research was that it was not feasible to have a third group that received only the well-being materials that are provided in conjunction with the face-to-face training to assess their impact independent of the impact of the training on parental well-being.

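### The primary model and the Table 2 simulations allow no hub-by-time variance, so the stated 80% power and the nominal 5% test hold only if that variance is zero

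*Protocol article*

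**What the plan says.** The Sample Size section of the protocol article specifies the primary model for key worker confidence (KWC): "The model will have random effects terms for hubs, key workers within hubs and assessments within key workers (within hubs"), with fixed effects for the four assessment times and for condition, fitted by REML. Its worked example splits a total variance of 18 into 2 for hubs, 4 for individuals and 12 for assessments within individuals. That uses the whole 18 and leaves nothing for hub-by-time. The simulations add one time element, a rise of 2 units over the study, as a safeguard against general improvement across the service.

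On the data, "we have made provision for between 6 and 8 key workers in each cluster to be repeatedly assessed across the periods", so "we expect to have between 144 and 192 observations of the primary outcome variable (KWC"). Trial Design adds: "All hubs are assessed at baseline and every 3 months thereafter". Table 2 gives minimum effects of 0.68, 0.56, 0.59 and 0.49, footnoted "Detectable with 80% power for the proposed stepped-wedge design with 6 hubs, 3 periods, and 4 assessment time points". The section concludes that "this study has moderate-to-high power to detect moderate effect sizes" for outcomes measured repeatedly on key workers.

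Trial Design reports a large amount of organizational change under way at the service. Strengths and Limitations says of the NDIS roll-out: "we anticipate will be a potential confounder on the outcome measurements".

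**The concern.** In this design a whole hub switches condition between two assessments, so the effect is estimated from contrasts among 24 hub-by-time cells. The model gives each hub one constant shift and treats the rest as worker-level variation. If all workers of a hub move together at one assessment for reasons unrelated to the program, that common movement is counted as 6 to 8 independent errors. The standard error is then too small, the F test rejects too often and the power figures are too favourable.

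Two features of the plan that look protective do not help here. The simulated 2-unit rise is common to all hubs, so the fixed time effects absorb it. The assumed between-hub variance of about 10% is constant over time, and it is largely removed because each hub serves as its own control. The component at the level where condition switches is set to zero. At stake are the primary p-value, its confidence interval and the closing power statement.

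**Working it through.** **Inputs.** From Sample Size, Table 1 and Table 2: 6 hubs; 4 assessments; two hubs exposed from 3 months, two more from 6 months and the last two from 9 months; n = 6 or 8 workers per hub; total variance 18; hub variance 2; individual/residual variance 4/12 (ICC 0.25) or 8/8 (ICC 0.5, since 18 − 2 = 16 is split equally). Assumed: two-sided alpha 0.05, which is not stated. One-sided 0.05 would give 0.44–0.61 and does not match Table 2.

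**Step 1: reproduce Table 2 with no hub-by-time variance.** The closed-form stepped-wedge variance of the condition effect on hub-by-time means is

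Var = I·s²(s² + T·t²) / [(IU − W)s² + (U² + ITU − TW − IV)t²],

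with s² = residual/n and t² = hub + individual/n. Here I = 6, T = 4, U = 12 exposed cells, W = 0 + 4 + 16 + 36 = 56 and V = 9 + 9 + 4 + 4 + 1 + 1 = 28. So IU − W = 16, and 144 + 288 − 224 − 168 = 40:

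Var = 6s²(s² + 4t²)/(16s² + 40t²); MDES = (1.960 + 0.842)·SE/√18.

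| n, ICC | s² | t² | Var | SE | MDES | Table 2 |
|---|---|---|---|---|---|---|
| 6, 0.25 | 2.000 | 2.667 | 1.096 | 1.047 | 0.691 | 0.68 |
| 6, 0.5 | 1.333 | 3.333 | 0.759 | 0.871 | 0.575 | 0.56 |
| 8, 0.25 | 1.500 | 2.500 | 0.835 | 0.914 | 0.603 | 0.59 |
| 8, 0.5 | 1.000 | 3.000 | 0.574 | 0.757 | 0.500 | 0.49 |

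Agreement is within 3%. Simulating the planned REML analysis (2000 trials per scenario, with the 2-unit trend) gives power of 0.798, 0.788, 0.792 and 0.791 at the Table 2 effects. Table 2 is therefore reproduced with hub-by-time variance at zero.

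**Step 2: move part of the hub variance to hub-by-time.** Let a share c of the hub variance of 2 vary over time, with the total kept at 18. Then s² = residual/n + 2c and t² = 2(1 − c) + individual/n. For c = 20%, n = 6, ICC 0.25: s² = 2.4, t² = 2.267, Var = 14.4 × 11.467/129.07 = 1.279, SE = 1.131 (8% higher), MDES = 0.747. For n = 8, ICC 0.5: s² = 1.4, t² = 2.6, Var = 8.4 × 11.8/126.4 = 0.784, SE = 0.886 (17% higher), MDES = 0.585.

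Power at the Table 2 effect d is Φ(d√18/SE − 1.960). Type I error is for the planned three-component model, simulated with no true effect. Ranges run over the four scenarios.

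| Share moved (variance; % of 18) | SE rise | MDES, normal | Power at Table 2 effects | Type I error, planned test | MDES, 14 df |
|---|---|---|---|---|---|
| 0% | – | 0.50–0.69 | 78–79% | 5.6–6.0% | 0.54–0.74 |
| 5% (0.1; 0.6%) | 2–5% | 0.52–0.71 | 75–77% | 6–7% | 0.56–0.76 |
| 10% (0.2; 1.1%) | 4–9% | 0.55–0.72 | 71–75% | about 7% | 0.59–0.78 |
| 20% (0.4; 2.2%) | 8–17% | 0.59–0.75 | 65–72% | 7–9% | 0.63–0.80 |
| 50% (1.0; 5.6%) | 18–37% | 0.68–0.81 | 52–65% | 10–14% | 0.74–0.88 |

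**Step 3: separate the two causes.** The last column uses 14 df (24 cells − 6 hubs − 3 time contrasts − 1 condition). With no hub-by-time variance at all, 14 df already gives 0.54–0.74. For n = 6, ICC 0.25 the path is 0.69 → 0.74 (df) → 0.80 (20% moved), so about half of that rise is due to df. The normal-quantile columns isolate the variance effect.

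**The case against.** The strongest reply is that everything here depends on a variance the documents do not give. A reader might infer that the F test is too liberal and Table 2 too optimistic as matters of fact. The article does not support that: Table 2 is correct for its declared inputs, and at 5% moved the loss is small (MDES 0.52–0.71). This stands, so the size can only be a range. The direction is the same for every positive value tried, and zero is the most favourable choice.

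A reader might also infer that the article reports shocks differing by hub. It does not. It describes change at the service and in the partner organization as a whole, and fixed time effects absorb what is common to all hubs. Hub-specific shifts are a reasonable inference, since sites may meet such change at different times and the first two hubs are chosen on readiness, but they remain an inference. Nor does the article claim that the 2-unit trend covers them.

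A third tempting reading is to quote 0.63–0.80 as the MDES caused by omitting this variance at 20%. That figure also contains the move to 14 df; the variance alone gives 0.59–0.75. Likewise, simulated power of 59–67% at 20% belongs to a replacement test on 14 df. And type I error was simulated at 5.6–6.0% with zero hub-by-time variance (1000 trials per cell), so the whole excess over 5% should not be charged to this term.

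Finally, the article states no df method and points to a separate analysis plan, and Quantitative Analysis leaves room to explore autocorrelation models. The df method may indeed be settled there. The random effects, however, are fixed in the article, and autocorrelation among a person's repeated measurements does not represent a shift shared by a whole hub.

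**Conclusion.** The point holds in conditional form. The primary model and the simulations behind Table 2 fix hub-by-time variance at zero in a design where condition varies only at that level. The stated 80% power and nominal 5% test rest on that value. If a fifth of the planned hub variance (2.2% of the total) varies over time, the detectable effect rises to about 0.59–0.75, power at the Table 2 effects falls to 65–72%, and the planned test rejects a true null about 7–9% of the time. At 5–10% moved the effects are modest; at 50% they are serious. These figures assume two-sided alpha 0.05, equal hub sizes, complete data and the plan's own variance components. The article supports neither the claim that the test is known to be invalid nor the claim that Table 2 was miscalculated. It does support saying that the power conclusion rests on an unacknowledged best case.

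**What to change.** Add a random hub-by-assessment-time term to the primary model and test condition with a small-sample correction such as Kenward-Roger. Report a regression of the 24 hub-by-time means on hub, time and condition (14 residual df) as a sensitivity analysis. It is not equivalent: fixing the hubs discards the between-hub information that Trial Design says will be used. Its variance is 0.6s², so for n = 6 and ICC 0.25 its SE is 1.095 against 1.047 with no hub-by-time variance, and 1.200 against 1.131 with 20% moved. In simulation it held type I error at 4.6–5.2%.

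Re-run Table 2 with 0%, 5%, 10%, 20% and 50% of the hub variance at hub-by-time level, state the df method used, and give the MDES as a range. Reword the power conclusion to match.

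The work is one model term, one df choice and a re-run of existing simulations. The price is a wider confidence interval, a less favourable MDES, and a variance that is poorly estimated with 6 hubs. The test may be somewhat conservative: the hub-by-time mixed model on 14 df gave simulated type I error of 2.5–4.7%.
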